## Abstract

**Background:** Home care programs in primary healthcare aim to address the health needs of elderly and frail populations, but ensuring safety in home environments can be challenging due to factors like limited supervision, environmental hazards, and the complexity of managing multiple health conditions. Fragmented information further complicates healthcare professionals’ ability to identify critical health risks and manage them effectively. **Objective:** This study aims to design and evaluate the effectiveness of a visual map integrated into the electronic medical record of home care patients. The goal will be to implement this tool and enhance healthcare professionals’ interventions, improving patient safety and quality of life. **Methods:** The study will be conducted in three phases: (1) the design of a visual map for the home care program by identifying health areas and contributing factors; (2) a cluster-randomized clinical trial across primary care centers to assess whether the visual map reduces hospital admissions, falls, and injuries while improving quality of life; and (3) a qualitative study to evaluate the impact of the visual map on the home care program. **Results:** It is anticipated that the visual map will reduce hospital admissions, falls, and injuries among home care patients while improving quality of life by facilitating targeted and effective professional interventions. **Discussion:** This visual map aims to enhance the safety of vulnerable home care patients by integrating critical health information into a practical, easy-to-implement tool. Its feasibility and potential for integration into routine primary care within the Catalan Institute of Health make it a valuable innovation with broader applicability. Trial registration: NCT04399616. Registered on 8 May 2024.

## 1. Introduction

In recent decades, rising life expectancy has contributed has contributed to a growing aging population in developed countries. In 2022, life expectancy at birth in Europe was 80.6 years, whereas in Spain, it reached 83.2 years [1]. Currently, nearly 20% of the Spanish population is aged 65 or older, a percentage that is projected to rise to 26% by 2037 [2]. Among this population, approximately 70% have chronic conditions, 26.3% have a disability, and 14% are dependent. Additionally, by the age of 75, more than half of the population (57.8%) experience disabilities and nearly 40% (38.5%) require assistance for daily activities, making their care a pressing challenge for healthcare systems [3].

Frailty, as defined in the “Conceptual bases and care model for frail people with complex chronicity or advanced chronicity” guides, is a multidimensional state of “vulnerability” to stressful factors. This occurs due to the limitation of compensatory mechanisms, putting the individual at a high risk of adverse health outcomes, such as disability, institutionalization, hospitalization, prolonged hospital stays, readmissions, falls, adverse reactions resulting from some specific interventions (for example, chemotherapy or surgeries), and, especially, increased mortality [4].

Managing the health and social needs of frail individuals is complex, requiring coordinated, patient-centered approaches. Consequently, home care programs have emerged as a solution, providing healthcare services in the patient’s home to enhance autonomy and improve quality of life [5].

Home care services, primarily delivered by home care nurses (HCNs), offer high-quality, patient-centered, and cost-effective care. A systematic review, which included a total of nine studies and involved a total of 46,154 individuals aged 65 and older, showed that home care programs reduce healthcare utilization and costs and improve both patient and caregiver satisfaction. Moreover, the review underscored the importance of interdisciplinary teams in coordinating complex patient care as a key driver of improved health outcomes [6]. However, the home environment presents unique challenges, necessitating active collaboration between patients, caregivers, and healthcare professionals [7]. Reliable and accurate information is essential for effective care planning, particularly in areas such as infection risk management [8].

Home care patients are more vulnerable to adverse events (AEs) due to conditions such as mental and physical deterioration, sensory deficits, polymedication, and a lack of professional or caregiver supervision. Despite this vulnerability, home remains the preferred setting for care, emphasizing the need for protocols to ensure patient safety [9].

A study conducted in Sweden found an AE incidence of 37.7%, with 76% considered preventable [10]. A review including studies comprising a pool of 168 articles from several countries reported AE rates ranging from 3.5% to 15.1% [11], similarly to a Canadian cohort of 1200 charts of clients from publicly funded home care programs in the 2009–2010 registry, which indicated an incidence of 4.2%, with 56% being preventable [12]. In all these studies, common AEs in home healthcare include falls, infections, behavioral issues, and medication-related complications [10,11,12]. According to AEs, a recent study concluded that home care patients have an increased likelihood of reporting potentially preventable AEs, particularly drug interactions [13].

Various interventions, such as exercise programs and home safety improvements, have been suggested to prevent AEs, particularly to reduce falls, and significantly improve mobility and activities of daily living in frail older adults [14,15]. Moreover, a Canadian study highlighted communication and team coordination as key factors that could ameliorate the contributing factors to AEs [16].

International initiatives, such as the “European Scaling-up Strategy in Active and Healthy Aging” initiative created by the European Commission, have aimed at the prevention and early diagnosis of frailty and functional decline [17]. For example, a community nursing program in Barcelona reduced healthcare utilization and mortality among older adults by promoting physical activity, proper nutrition, and medication management [18].

The population that is elderly and frail, or at risk of becoming so, need advice focused on their circumstances from HCNs with the aim of preserving their autonomy, improving their quality of life, avoiding AEs, and reducing mental and physical deterioration. By identifying certain factors, proactive actions could be taken to prevent or reduce frailty and improve health and quality of life [9,19]. In Germany, an intervention based on nurse and physician training and the use of a software tool aimed to reduce adverse drug events in home care patients [20]. In Canada, integrative software was used to support person-centered care, clinical and management processes, and proactive care in the home care environment [21].

Despite the availability of extensive patient information in medical records, covering risk areas such as falls, infections, medication safety, caregiver support, autonomy, symptom control, and social determinants, this information remains fragmented across different records. This fragmentation hinders HCNs from quickly identifying critical health concerns and prioritizing patient safety. However, there is a notable gap in the literature regarding the use of information and communication technologies to streamline patient risk identification in home care settings.

To address this issue, the present study leverages information and communication technologies to develop a visual alert map that consolidates key patient data. By translating medical records into an accessible format, this tool aims to enhance HCN practices, facilitate prioritization, and reduce AEs in home care.

## 2. Materials and Methods

### 2.1. Aim of Study

This project’s overall aim is to design, implement, and evaluate the effectiveness of a visual map available in the EMRs of home care patients with the goal of enhancing HCN interventions to improve their safety and quality of life.

The specific objectives of the study are as follows:Develop a visual map to be integrated into EMRs, ensuring that it effectively organizes and prioritizes key patient health information.Assess the effectiveness of the visual map in improving patient safety and care coordination through a cluster-randomized clinical trial conducted in primary care centers in the countryside of Tarragona, Spain.Explore healthcare professionals’ perceptions of the visual map’s impact on home care practices through a qualitative study, identifying strengths, challenges, and areas for improvement.

### 2.2. Setting of the Study

Patients at primary care centers in Tarragona (Spain) that belong to the Catalan Health Institute will be included in the home care program.

This area is represented by 20 primary care team, distributed in 20 primary care centers and more than 70 local clinics, serving a home care population of 3244 users.

### 2.3. Study Development

The general framework of this study is shown in Figure 1. In general, the study includes three phases, each corresponding to a specific objective:Phase (1): the design of the visual map included in the home care program.Phase (2): a cluster-randomized clinical trial across different primary care centers in the countryside of Tarragona, Spain.Phase (3): a qualitative study to evaluate the impact of the visual map’s implementation in the home care program by healthcare professionals.

#### 2.3.1. Phase 1: Design of Home Care Visual Map

The first phase consists of designing a tool based on a visual map available in the EMRs of home care patients.

In this way, the professionals who attend to home care patients will have immediate access to the visual map including the main health areas related to each patient. This phase includes two sub-phases: the identification of health areas and their contributing factors.

Identification of health areas and their contributing factors

First, a group of experts specializing in home care programs and chronic health conditions will be formed. This group will search and discuss the variables available in EMRs that can act as risk factors and classify them into different health areas.

The selection of the variables will be based on data analysis, discussion, and consensus among the experts. The agreed health areas will constitute the visual map. An example of a visual map with health areas and their contributing factors is shown in Figure 2.

2.Risk weighting with a group of experts

Once the health areas and their contributing factors are identified, the risk or problem per area will be weighted as follows: no risk (in green), potential risk (in orange), and current problem (in red). This weighting will be take into account the magnitude or severity of the measured problem. An example of the visual map with risk weighting is shown in Figure 3.

The research team will form a group of experts for each area and the cut-off points will be decided to classify the risk.

Finally, all this information will be registered and integrated into EMRs.

#### 2.3.2. Phase 2: Cluster-Randomized Clinical Trial Across Different Primary Care Centers in Countryside of Tarragona, Spain

A cluster-randomized clinical trial will be carried out for 12 months. The study will be conducted in 20 primary care centers in the Tarragona area. These centers will be randomly allocated into two groups at a ratio of 1:1. The intervention group will have the home care visual map available. No blinding will be implemented in this study. This open-label design is chosen due to the nature of the interventions, which will make blinding unfeasible

This phase of this study will follow the SPIRIT Statement guidelines for reporting clinical trial protocols.

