##### Variables

The main outcome variables of this study are as follows:The proportion of patients with hospital admissions and avoidable hospital emergency visits (main variable) during the follow-up period.The percentage of patients with ulcers and falls.The total number of avoidable admissions and hospital emergency visits during the follow-up period.The total number of deaths and definitive institutionalizations.Quality of life, measured using the EuroQol-5D index, a record currently available in EMRs [22].

The following are considered as covariates:Age, sex, and socio-economic level [23] and the home care model.Main comorbidities, following the Charlson comorbidity index [24].

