##### Data Collection and Sources of Information

Most of the data will be collected from EMRs, such as socio-demographic variables and scores on the different scales. Other sources of information will be direct observation, interviews with patients and caregivers, and exchange of information with other HCNs involved, such as HCNs from social services or other healthcare facilities.

To promote participant retention and complete follow-up, monthly sessions will be held to assess the progress of this study. During these sessions, the study’s advancement will be discussed, and any concerns or deviations from the intervention protocol will be addressed.

Study data will be collected and managed using REDCap electronic data-capture tools hosted at Camp de Tarragona of the Catalan Institute of Health [25,26]. REDCap (Research Electronic Data Capture) is a secure, web-based software platform designed to support data capture for research studies, providing (1) an intuitive interface for validated data capture; (2) audit trails for tracking data manipulation and export procedures; (3) automated export procedures for seamless data downloads to common statistical packages; and (4) procedures for data integration and interoperability with external sources.

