##### Data Analysis

Continuum variables will be described using means and standard deviations if they follow a normal distribution or using means and interquartile ranges otherwise. The normality of the variables will be described using the Kolmogorov test. Categorical variables will be described with percentages and 95% confidence intervals.

Outcomes will be compared between groups using the Chi-square test. A multivariate analysis (Cox regression) will be performed, introducing adjustment variables into the model: socio-demographic variables, risk areas, and covariates, as mentioned before. Covariate selection will be based on clinical relevance and statistical significance (*p* < 0.05 in univariate analysis or established predictors from previous research). The time until the event of the main outcome variables will be considered in the model.

For the “quality of life” outcome, the test scores (averages and percentiles) will be compared between the control and intervention groups at the beginning and at the end of the intervention using the *t* test.

Missing data will be handled under the principle of the worst-case scenario. However, different imputation strategies may be considered depending on the context.

The statistical package R (R foundation for statistical computing, Vienna, Austria; version 4.1.2 or later) will be used for all analyses. Statistical significance shall be established at *p* < 0.05.

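### The protocol rules out all blinding for a reason that covers only professionals and patients, leaving any judgement of avoidability and the open analysis choices unmasked

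*Protocol article*

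**What the plan says.** The protocol article, section 2.3.2, states for the whole of Phase 2: "No blinding will be implemented in this study". The justification follows at once: "This open-label design is chosen due to the nature of the interventions, which will make blinding unfeasible".

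The Variables subsection defines the main outcome as "The proportion of patients with hospital admissions and avoidable hospital emergency visits (main variable) during the follow-up period". A further outcome carries the same qualifier: "The total number of avoidable admissions and hospital emergency visits during the follow-up period". The article does not say how a visit or admission comes to be called avoidable.

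The Data Collection and Sources of Information subsection takes most data from the electronic record and then adds: "Other sources of information will be direct observation, interviews with patients and caregivers, and exchange of information with other HCNs involved".

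The Data Analysis subsection compares outcomes with a Chi-square test and adds a Cox model. For that model, "Covariate selection will be based on clinical relevance and statistical significance", where significance means p < 0.05 in univariate analysis, with predictors known from earlier research as an alternative route. Missing data default to a worst-case rule, but "different imputation strategies may be considered depending on the context".

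**The concern.** The conclusion is wider than its reason. A map shown in the electronic record cannot be hidden from the professionals who use it, and their patients may learn of it. Nothing about the map prevents an outcome classifier from working on records without centre and arm, or an analyst from working with coded arms.

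This is a stated rule and not a detail left out for brevity. An analysis plan that introduced masking would have to depart from the sentence as written.

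Two things could be affected. The first is the emergency-visit part of the main variable: routine records establish that a visit took place, but not that it was avoidable. The second is the analysis choices that the article leaves open. If either is settled by someone who knows the arm, the result can move towards the expected benefit without any true effect.

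**Working it through.** No figure in the plan measures this bias, so there is none to reproduce. The check sets the statements side by side and then shows what size a shift might have under assumed inputs.

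**1. Who the stated reason covers**

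| Role | Does the nature of the intervention prevent masking? |
|---|---|
| Professionals using the map | Yes |
| Patients | At most in part |
| Whoever assigns the avoidable label | No |
| Analyst | No |

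The plan nevertheless applies the exclusion to all four.

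**2. Which part of the main variable is exposed**

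As worded, the qualifier attaches to emergency visits and not to admissions. Whether a patient was admitted is largely objective. If the main variable counts a patient with either event, the label matters only for patients with an emergency visit and no admission.

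**3. Illustration**

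Assumed inputs, none of them from the document:
- share of patients with only an emergency visit: 15%
- proportion of those visits called avoidable: 50% in control, 35% in intervention
- no true effect, and either event counts

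Shift = share with only a visit × difference in labelling = 0.15 × (0.50 − 0.35) = 0.0225, or about 2.3 points.

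**4. Is the 15% share compatible with the plan?**

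The Sample Size subsection gives a baseline admission rate of 65.89%. If that is the share of patients admitted, 100 − 65.89 = 34.11% have no admission. A 15% share then requires 15 / 34.11 = 44% of those patients to have an emergency visit. That is possible, but the document cannot confirm it.

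**5. Comparison with the target**

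The target is a 10% reduction, stated for admissions and without saying whether it is absolute or relative.
- Absolute: 10 points, so the shift is 2.25 / 10 = about 23% of it.
- Relative: 0.10 × 65.89 = about 6.6 points, so the shift is 2.25 / 6.59 = about 34% of it.

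**6. Effect on false-positive risk**

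Taking the planned 272 per group less 15% loss (272 × 0.85 = about 231), an event rate of 65.89% and independent patients, a spurious shift of 2 points raises two-sided rejection under no effect from 5% to about 7%. A shift of 3 points raises it to about 10%. These figures ignore the clustering by centre and are only a guide.

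**7. Which analysis choices are exposed**

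The Chi-square comparison takes no covariates, so covariate selection cannot alter it. Selection does affect the Cox model, and the univariate p-value criterion can be applied only once outcome data exist. The imputation clause could affect any analysis with missing outcomes. The article does not say when that choice would be made, and nothing in it keeps the arm from the person who makes it.

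**The case against.** The strongest reply is that no part of the article says a person judges avoidability. Most data come from the electronic record, and a code list or triage rule applied to it would leave little for knowledge of the arm to influence. An article may also leave the operational definition to the full protocol. This stands. The harm to the main variable is conditional on the label involving judgement and cannot be asserted as fact.

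A reader might infer that the whole main variable is subjective. The wording does not support that, because admissions carry no qualifier there. The separate count of avoidable admissions and visits does use the label more broadly, but it is not the main variable.

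A reader might also infer a bias close to the target effect. For example, 30% of patients with only a visit and a labelling split of 50% against 30% would give 0.30 × 0.20 = 6 points. On the plan's own admission figure this needs 30 / 34.11 = 88% of the non-admitted patients to have an emergency visit, so it should not be used. Even the 2.3-point illustration depends on reading the main variable as either event. If both were required, patients with only a visit would not count and the calculated shift would be zero.

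On the analysis choices, the reply is that the covariate criteria and a missing-data default are stated, and that final details belong to an analysis plan that is not shown. That is fair, and their absence is not the complaint. What remains is that the p-value selection and the open imputation clause are written into this article, next to a statement that nobody will be blinded. Masking would not cure every weakness of selecting covariates by p-value, but it would stop the choice from being steered by the arm comparison.

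**Conclusion.** The point holds in limited form. The exclusion of all blinding is broader than the reason given for it and should be narrowed.

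- The emergency-visit part of the main variable is exposed if, and only if, the avoidable label involves judgement. The admission part is largely protected.
- The p-value covariate selection for the Cox model and the option to change the imputation strategy would be exercised with the arm known. The Chi-square comparison is not touched by covariate selection.
- The size of any bias cannot be derived from the document. The 2.3-point shift rests wholly on assumed shares, an either-event reading and the absence of a true effect. It compares with a target of 10 points if absolute or about 6.6 if relative.

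The documents do not show that bias will occur. They show that an inexpensive protection was ruled out without a reason that applies to it.

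**What to change.** Replace the blanket sentence in section 2.3.2 with wording such as:

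> Professionals and patients are not blinded. Avoidability is assigned by a pre-specified rule applied to extracts with centre and arm removed; any case needing judgement is classified by existing study staff on the same masked extracts. The analyst works with masked arm codes until the covariates, the missing-data method and the code for the main variable are locked.

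Because allocation is by centre, any centre identifier that the analyst needs should also be a neutral code.

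The cost is one protocol change and a small data-management step before analysis. REDCap, already named in the Data Collection and Sources of Information subsection, is described there as supporting automated exports. If some visits need manual classification, existing staff will spend some time on it. Open-label care and the pragmatic design are unchanged.
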